**A phase II, open-label, single-arm, multi-center study of Sintilimab, stereotactic body radiotherapy and granulocyte-macrophage colony stimulating factor in advanced non-small cell lung cancer (SWORD)**

# Lung cancer is one of the most common cancers worldwide and there are approximately 1.8 million new cases by 2012, representing 12.9% of all new cancers^[1]^. It is also the most common cause of deaths from cancer, accounting for 19.4% of all cancer-attributed deaths^[2]^. Non-small cell lung cancer (NSCLC) represents 80% to 85% of lung cancers. Unfortunately, approximately 50% of NSCLC patients already have advanced disease at the time of diagnosis. Treatment options for advanced NSCLC patients are very limited after the failure of first-line therapy and the prognosis of these patients is dismal, with a 5-year overall survival (OS) rate less than 10%^[4, 5]^.

Especially, advanced NSCLC patients without driver mutations have few effective drugs. Targeted therapy has significantly improved the survival of metastatic NSCLC patients with driver mutations, such as epidermal growth factor receptor (EGFR) mutations, anaplastic lymphoma kinase (ALK) translocations and ROS proto-oncogene 1 (ROS1) translocations. Tyrosine kinase inhibitors (TKIs) have been established as standard first-line treatments for these patients with driver mutations, with a median OS of more than 30 months^[6]^. However, treatments for advanced NSCLC without driver mutations remain an urgent unmet need. For these patients, the median OS is about 11 months. Even with maintenance chemotherapy, it is only increased by about 2 months^[7]^. Since the majority advanced NSCLC patients have no targetable driver mutations, it is of great clinical significance to improve both the survival and quality of life in these patients.

As early as 1953, Mole et al. observed the regression of tumor outside the irradiated field, and called it the abscopal effect^[8]^. Recently, the mechanisms underlying the immune-regulatory effects of radiotherapy have been illucidated. Radiotherapy induces immunogenic cell death (ICD) of tumor cells and causes the release of tumor associated antigens, dAMP and cytokines, which stimulates the maturation of dendritic cells (DCs). Mature DCs present tumor antigens to T cells. Then T cells are activated and expanded into tumor-specific T cells, thereby producing anti-tumor immune effects^[9]^. Radiotherapy also induces the up-regulation of major histocompatibility complex-I (MHC-I), which plays a crucial role in the activation of T cells^[10]^. Radiotherapy can also induce the up-regulation of tumor-associated antigens on the tumor cell membrane, thus enabling the immune system to recognize tumor cells more effectively^[9]^. In addition, radiotherapy alters the MHC-I-associated peptide profiles, some of which can only be induced specifically by radiation, recognized as "foreign peptide"(neoantigen) by the immune system^[10]^. These mechanisms lead to the use of radiotherapy as an *in-situ* tumor vaccine, which stimulates specific anti-tumor immunity to kill tumors outside the irradiated field. However, radiotherapy using conventional fractionation is not potent enough to stimulate sufficient immune cells to infiltrate the tumor sites. As the body has an effective set of immunosuppressive mechanism to prevent autoimmunity, it also greatly limits the anti-tumor immune effect, which partially explains why the abscopal effect is rare when radiotherapy of conventional fractionation is used alone^[11]^.

Stereotactic Body Radiation Therapy (SBRT) is a technique for delivering high doses of radiation to tumors while preserving the normal tissues located around this area. In addition to effectively killing tumor cells in the irradiated field, SBRT can also mediate immune response and cause the regression of un-irradiated lesions. SBRT increases the fractional dose and reduces the number of exposures. It also has higher conformability to the tumor and less damage to the surrounding tissues. Its larger local dose causes the irradiated tumor cells to release more tumor-associated antigens. Meanwhile, the lymphatic tissues around the tumor get better protection. These makes SBRT more effective in inducing anti-tumor immunity. The concept of iSABR has been put forward in 2016, which suggests that SABR can stimulate the immune response more effectively than conventional fractional radiotherapy based on preclinical evidence and clinical data, and points out the important research value of the combination of iSABR with other therapies^[12]^. In a phase I study of ipilimumab combined with SBRT (single dose 6Gy-12.5Gy, total dose 50-60Gy) for malignant melanoma, 31 out of the 35 patients enrolled did not progress in the out-of-field lesions, including 3 (10%) partial response (PR), and 7 (23%) having clinical benefit [PR or stable disease (SD)] for more than 6 months^[13]^. A meta-analysis of 14 studies on the abscopal effects of radiotherapy in murine model showed that the incidence of abscopal effects increased as the biological equivalent dose (BED) of the irradiated tumor elevated^[14]^.

Immune checkpoint inhibition (ICI) has revolutionized the treatment landscape of advanced NSCLC. Programmed cell-death protein 1 (PD-1) is an immune checkpoint molecule. PD-L1 and PD-L2, the ligands of PD-1, are up-regulated in a variety of tumor cells and tumor infiltrating cells. The interaction of PD-1 and its ligands (mainly PD-L1) can lead to the inhibition of cytotoxic T cells and the enhancement of regulatory T cells (Tregs), thereby inhibiting anti-tumor immunity. Sintilimab, a fully humanized anti-PD-1 monoclonal antibody, can block the interaction between PD-1 and PD-L1/PD-L2, subsequently induce strong anti-tumor response, which has confirmed *in vitro* and *in vivo*, with comparable affinity, pharmacokinetic characteristics and safety to pembrolizumab and nivolumab. For NSCLC, PD-1 monoclonal antibody nivolumab and pembrolizumab, as well as PD-L1 monoclonal antibody, atezolizumab and durvalumab, have all shown significant survival benefits when compared with the current standard of care treatments^[17-21]^. In the Keynote001 study, the ORR of pembrolizumab was 24.8% in untreated patients and 18.0% in previously-treated patients^[21]^. In the Keynote010 study, 1034 previously-treated advanced NSCLC patients were enrolled and divided into docetaxel group, low-dose pembrolizumab group and high-dose pembrolizumab group. An improved OS was observed in the high-dose pembrolizumab group compared with the low-dose pembrolizumab group and the docetaxel group (12.7 months vs 10.4 months vs. 8.5 months)^[22]^. In the PACIFIC study, durvalumab was used for unresectable stage III NSCLC without progression after standard platinum-based concurrent chemoradiotherapy. Durvalumab maintenance significantly prolonged PFS and OS compared with placebo^[20]^. However, the treatment efficacy of PD-1/PD-L1 inhibitors alone in unselected advanced NSCLC remain limited, with an ORR around 15%-20%, highlighting the crucial needs for the development of novel combinational treatment strategies with higher potency and less toxicity.

Based on the above data, we hypothesized that sintilimab combined with radiotherapy may have a synergistic effect in promoting anti-tumor immune effect, which has been initially manifested in similar drugs. In a case report where a patient with stage IIIB NSCLC received SBRT in combination with nivolumab, the irradiated tumors, as well as the metastatic lymph nodes outside the irradiation field, all reached CR^[15]^. The abscopal effect was also observed in two patients with metastatic skin Merkel cell carcinoma who were treated with the combination of pembrolizumab and single-dose palliative radiotherapy^[16]^. However, the feasibility and efficacy of sintilimab and SBRT in advanced NSCLC remain undetermined.

Granulocyte-macrophage Colony Stimulating Factor (GM-CSF) is a hematopoietic growth factor that can promote the differentiation, maturation, and expansion of DCs and enhance their ability to recognize and process tumor antigens and present tumor antigens to T cells, thereby promoting anti-tumor immune responses. Mature DCs are critical in generating anti-tumor immune response. Compared with immature DCs, mature DCs have membrane receptors that mediate the uptake of antigens such as Fc receptors, giving these cells stronger capabilities of uptaking and processing antigens. Mature DCs also have a high level of MHC-II molecules, costimulatory molecules, and adhesion molecules, which improves their antigen presentation ability. Since GM-CSF promotes the maturation of DCs, it is theoretically effective in promoting anti-tumor immune response. Preclinical studies have found that the irradiated malignant melanoma cell is insufficient to produce anti-tumor immune effects, while the concurrent use of retrovirus which could secret GM-CSF enables the melanoma cell to produce strong and long-lasting anti-tumor immunity^[23]^. In a clinical study where 41 patients with metastatic malignant tumors were treated with radiotherapy combined with GM-CSF, abscopal effect were seen in 11 patients (26.8%), and it was particularly significant that 4 out of the 11 NSCLC cases had objective response out-of-field ( 2 CR at the remote sites). Furthermore, patients with abscopal effect was found to have longer OS. As no dose reduction or treatment interruption occurred due to treatment related toxicity, the combination of GM-CSF and radiotherapy is considered a safe treatment for inducing anti-tumor immune effects^[24]^. Another study enrolling 72 lung cancer and 54 esophageal cancer patients examined the serum levels of GM-CSF before and during radiotherapy, and found that patients with elevated level of serum GM-CSF after radiotherapy had significantly prolonged PFS and OS^[25]^. Taken together, we hypothesized that the combination of SBRT and GM-CSF may bring survival benefits in advanced NSCLC.

In summary, the combined application of SBRT, sintilimab, and GM-CSF may enhance the effect of immunotherapy, thereby improving the clinical efficacy in advanced NSCLC. So far, there have been no prospective studies to confirm this scientific hypothesis, as well as the clinical value of the combination therapy. Therefore, we plan to carry out a phase II study of SBRT combined with sintilimab and GM-CSF in the treatment of advanced NSCLC, attempting to explore the feasibility of this triple therapy which mechanically could enhance anti-tumor immune response through promotion of both innate and adaptive immune processes.

1. Study objectives

To explore the safety and preliminary efficacy of SBRT combined with sintilimab and GM-CSF in stage IV NSCLC patients without driver mutations such as EGFR, ALK, and ROS1.

**2.1 Primary objective:**

**Overall Response Rate (ORR):** Tumor response is evaluated by investigators according to the Response Evaluation Criteria in Solid Tumors (RECIST) 1.1. ORR is defined as the proportion of patients who experienced CR or PR as the best response in the total evaluable cases.

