**2.2 Secondary objectives:**

**Treatment-related adverse events (TRAEs):** The proportion of the treatment-related toxic reactions in the total evaluable cases according to the Common Terminology Criteria Adverse Events (CTCAE) 5.0.

**Out-of-field (abscopal) response rate (ASR):** At any time through enrollment to last follow-up, the longest diameter of any un-irradiated target lesions (per RECIST v1.1) reduce ≥30% will be considered as out-of-field (abscopal) response. The ASR is defined as the proportion of patients with an out-of-field response in the total evaluable patients.

**Overall survival (OS):** The time interval from enrollment to death due to any cause. Patients who are still alive at the time of analysis will be censored at the date of last contact.

**Progression free survival (PFS):** The time interval from enrollment to the first documented disease progression or death due to any cause. Patients who are still alive without disease progression at the time of analysis will be censored at the last date of last radiographic follow-up.

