**3.1 Inclusion criteria:**

Subjects must meet all of the following inclusion criteria to participate in this study.

1. Age ≥ 18 years old.
2. ECOG performance status 0-1.
3. Histologic or cytologic confirmed NSCLC, stage IV (AJCC 8th).
4. Driver mutations (including EGFR, ALK, and ROS-1) negative.
5. Disease progressed after first-line platinum-based chemotherapy (excluding anti-PD-1/PD-L1 therapy).
6. Subjects with stable or asymptomatic brain metastases can be included, but they must have stable lesions and no neurological symptoms without receiving systemic glucocorticoid therapy.
7. At least 1 lesion with a longest diameter of 1-5cm which was suitable for SBRT at a dose of 24Gy/3Fx, and at least 1 evaluable (RECIST1.1) lesion other than the one to receive SBRT. Lymph nodes can be selected as independent evaluable lesions and SBRT lesions, while brain metastasis cannot be chosen as either SBRT or out-of-field evaluable lesions.
8. Previous radiotherapy is permitted as long as the following conditions were met: 1) SBRT and out-of-field evaluation evaluable lesions must have not received previous radiotherapy; 2) dose received at normal tissue will not be affected by the previous radiotherapy. (Note: If the subject has received previous radiotherapy, detailed radiotherapy-related parameter data should be provided).
9. No palliative radiotherapy was required during study period per investigators’ judgment.
10. Subject who has undergone surgery must fully recover from the toxicity and complications of the surgery before starting treatment.
11. Subjects are encouraged to provide serial blood and tissue samples before and during treatment per protocol requirements.
12. Males/females of child-bearing age should agree to contraception during the trial (surgical ligation or oral contraceptives/intrauterine contraceptives + condoms).
13. Life expectancy ≥ 3 months.
14. Organ function reached the following standards within one week before enrollment:
15. Bone marrow function: hemoglobin ≥ 80 g/L, white blood cell count ≥ 4.0 * 10^9/L or neutrophil count ≥ 1.5 * 10^9/L, platelet count ≥ 100 * 10^9/L;
16. Liver: Serum total bilirubin level ≤ 1.5 times the upper limit of normal (ULN), and aspartate aminotransferase (AST) and alanine aminotransferase (ALT) ≤ 2.5 times ULN. For serum total bilirubin level > 1.5 times ULN, the direct bilirubin level must ≤ ULN;

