**Figure 1. Study flow**

**Table 1. Study schedule**

|  | **Baseline screening** | **SBRT** | **Sintilimab, GM-CSF treatment** | **Sintilimab maintenance** | | **End of treatment**  **Survival follow-up** |
| --- | --- | --- | --- | --- | --- | --- |
| Window (days) | Within 28 days before the start of SBRT | End of SBRT  (or before D1 administration) | C1D1  D5/9/14 (± 2 days) | C2D1  (±3 days) evaluation before each administration | CnD1  (±3 days) | Every 3 months  (±7 days) |
| Frequency |  |  | 3 times in total | Every 3 weeks | Every 9 weeks  (every 3courses of Sintilimab) | Every 3 months |
| **Research procedure** |  | | | | | |
| Informed consent^1^ | X |  |  |  |  |  |
| Inclusion criteria | X |  |  |  |  |  |
| Demography/ Medical history/ Previous treatments^2^ | X |  |  |  |  |  |
| Vital signs ^3^ |  |  |  |  |  |  |
| Weight/Height^4^ | X |  |  | X | X |  |
| Medical history^5^/ Physical examination | X |  | X | X | X | X |
| ECOG PS score | X |  |  | X | X | X |
| Blood routine ^6^ | X |  | X | X | X | X |
| Coagulation function ^7^ | X |  |  | X | X | X |
| Blood Biochemistry ^8^ | X |  | X | X | X | X |
| Thyroid function ^9^ | X |  |  | X | X | X |
| Pregnancy test ^10^ | X |  |  |  |  |  |
| Urinalysis ^11^ | X |  |  | X | X |  |
| Virological antibody testing (HIV, HBV and  HCV) | X |  |  |  |  |  |
| 12-lead ECG | X | when necessary | | | | |
| Lung function | X |  |  |  |  |  |
| Adverse event assessment ^12^ |  | X | X | X | X | X |
| Concomitant medication | X | X | X | X | X | X |
| Subsequent anti-tumor treatment |  |  |  |  |  | X |
| Telephone follow-up (when outpatient follow-up is not possible) |  |  |  |  |  | X |
| **Efficacy evaluation** |  | | | | | |
| Radiographic assessment ^13^ | X |  |  |  | X | X |
| Gene mutation detection ^14^ | X |  |  |  |  |  |
| **Biomarker exploration** |  | | | | | |
| Blood specimens for biomarker studies ^15^ | X | X (end of SBRT) | X | X | X | X |
| Tumor puncture ^16^ | X | X (end of SBRT)  (Recommended, not required) | X (after d14 GM-CSF medication,  Recommended, not required) |  |  |  |

1. The signing of the ICF should be performed before any study procedure.
2. Previous treatments include treatment for the initial diagnosis, including chemotherapy, radiotherapy, and surgical treatment, as well as treatment for previous co-existing diseases within the past 30 days.
3. Vital signs include temperature, pulse, respiratory rate, and blood pressure.

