**The principle of lesion selection:**

1. Try to choose lesions with less damage to normal tissues.
2. Try to choose the largest one among all the available lesions, but the size should not exceed 5cm.
3. For bone metastases, if there is no obvious soft tissue mass, they should not be selected for SBRT.
4. Brain metastases should not be selected for SBRT treatment.
5. The lesions that are easier to undergo biopsy should be kept for biopsy, and not be selected for SBRT.

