**6 Statistical analysis**

**6.1 Calculation of sample size**

This study uses the objective response rate (ORR) as the primary end point. This single-arm study requires 56 eligible patients. Considering a 10% dropout rate, a total of 63 patients will be enrolled.

The research hypothesis is based on Checkmate 017 and Checkmate 057 study, which reported an ORR of 20%. If the ORR of the experimental treatment in this study is 20%, it is not worthy of further study. But if the ORR of the experimental treatment in this study is 38%, the study is considered successful. The purpose of this study is to distinguish ORR between 20% and 38%. The statistical assumptions are: the null hypothesis ORR<=20%, and the opposite hypothesis ORR>=38%. If 17 or more of the 56 eligible patients are CR or PR, this study is deemed successful and is worthy of further study. With a one-sided type one error rate (alpha) equal to 0.0432, this study has at least 90% statistical power to reject the null hypothesis.

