**6.5 Study Endpoint**

**6.5.1 Primary endpoint**

**Overall response rate (ORR):** The ratio of the total number of patients achieving CR or PR to the total number of evaluable cases according to the RECIST1.1. The data will be expressed as a two-sided confidence interval.

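### The primary ORR does not keep the irradiated lesion out of the target lesions, while its 20% null comes from PD-1 antibody trials, so endpoint and null are not like-for-like

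*Protocol*

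**What the plan says.** **Primary endpoint.** Protocol section 2.1 states that "Tumor response is evaluated by investigators according to the Response Evaluation Criteria in Solid Tumors (RECIST) 1.1". Section 6.5.1 gives it as "The ratio of the total number of patients achieving CR or PR to the total number of evaluable cases according to the RECIST1.1". Neither says whether the irradiated lesion may be a target lesion.

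**Abscopal response rate (secondary).** Section 2.2 counts a response when "the longest diameter of any un-irradiated target lesions (per RECIST v1.1) reduce ≥30" per cent, and section 6.5.2 has the same restriction. The irradiated/un-irradiated distinction is thus made for this endpoint and not for the primary one.

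**Choice of the SBRT lesion.** The selection principles in section 5.1 say "Try to choose the largest one among all the available lesions, but the size should not exceed 5cm". They also ask for sparing of normal tissue and for easily biopsied lesions to be left for biopsy. Inclusion item 7 sets the size at 1-5 cm and requires "at least 1 evaluable (RECIST1.1) lesion other than the one to receive SBRT".

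**Baseline.** Table 1 places screening, including imaging, "Within 28 days before the start of SBRT". The next scheduled imaging is during sintilimab, every three courses.

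**Local effect.** The background says of SBRT "In addition to effectively killing tumor cells in the irradiated field" that it can also act on un-irradiated lesions. It gives no in-field response rate.

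**Null and rule.** Section 6.1 says "The research hypothesis is based on Checkmate 017 and Checkmate 057 study, which reported an ORR of 20" per cent. It sets 20% against 38%, calls the study successful at 17 or more responders in 56, and states a one-sided alpha of 0.0432 and power of at least 90%.

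**The concern.** A one-sample test against a historical rate is only as good as the match between what was measured then and what is measured now. Here one lesion receives a direct local treatment after baseline and nothing stops its diameter from entering the response sum. The benchmark comes from trials of a PD-1 antibody, where no measured lesion was treated in this way. Section 6.1 does not describe those trials. That they were drug-only follows from the reference list, which has two nivolumab-versus-docetaxel trials, and from the background, which puts ORR at 15%-20% for PD-1/PD-L1 inhibitors alone.

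The error runs in one direction: in-field shrinkage can only help a patient meet the PR threshold. At stake is the meaning of the 17/56 decision. The stated rationale for the combination is a stronger anti-tumor immune response, including against tumors outside the irradiated field. A positive result could arise without that.

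**Working it through.** **1. Reproduce the stated design.** Inputs from section 6.1: n = 56, cut-off 17, p0 = 0.20, p1 = 0.38, dropout 10%. Exact binomial:
- P(X ≥ 17 | 56, 0.20) = 0.0432, as stated.
- P(X ≥ 17 | 56, 0.38) = 0.908, consistent with at least 90%.
- 56 / 0.90 = 62.2, so 63 enrolled, as stated.

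The arithmetic of section 6.1 is correct. The question is what the rule tests.

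**2. Can the SBRT lesion alone produce a PR?** Take PR as a 30% fall in the sum of target-lesion diameters. Let Ls be the SBRT lesion and Lo the sum of the others, unchanged. Required in-field shrinkage = 0.30 × (Ls + Lo) / Ls.

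| SBRT lesion + others (cm) | Calculation | Shrinkage needed |
|---|---|---|
| 5 + 1 | 0.30 × 6/5 | 36% |
| 5 + 2 | 0.30 × 7/5 | 42% |
| 4 + 2 | 0.30 × 6/4 | 45% |
| 3 + 3 | 0.30 × 6/3 | 60% |
| 5 + 3 + 2 | 0.30 × 10/5 | 60% |
| 3 + 4 + 4 | 0.30 × 11/3 | 110%, impossible |

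With few lesions and a dominant SBRT lesion, moderate local shrinkage suffices. If the SBRT lesion is under 30% of the sum, it cannot produce a PR alone.

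**3. Effect on the decision.** Assume that a fraction q of systemic non-responders become PR through the SBRT lesion only, with the systemic ORR held at 20%. Then ORR = 0.20 + 0.80q, and expected local PRs in 56 = 56 × 0.80 × q = 44.8q. The documents give no value for q, so a range is shown.

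| q (assumed) | ORR | Expected local PRs | P(X ≥ 17 of 56) |
|---|---|---|---|
| 0 | 20% | 0 | 0.043 |
| 2.5% | 22% | 1.1 | 0.092 |
| 5% | 24% | 2.2 | 0.168 |
| 10% | 28% | 4.5 | 0.396 |
| 15% | 32% | 6.7 | 0.652 |

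At 20%, 56 × 0.20 = 11.2 responders are expected. About six local PRs (17 − 11.2 = 5.8) make up the difference to the cut-off.

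**4. The two consistent designs.**
- SBRT lesion excluded: 20% is a like-for-like null and 17/56 keeps alpha 0.0432. Power stays at 0.908 only if 38% is still the target for out-of-field response.
- SBRT lesion kept: the null should carry the local contribution. With n = 56, alpha at most 0.05 and assumed nulls:

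| Assumed null | Cut-off | Alpha | Power at 38% |
|---|---|---|---|
| 25% | 20/56 | 0.0486 | 0.685 |
| 28% | 22/56 | 0.0448 | 0.471 |
| 30% | 24/56 | 0.0280 | 0.268 |

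**The case against.** The strongest reply is that the stated objective is the safety and preliminary efficacy of the combination, that section 6.1 tests the ORR of the experimental treatment, and that SBRT is part of that treatment. Whole-regimen ORR with a separate out-of-field secondary endpoint is a legitimate phase II choice. This stands as far as the endpoint goes. It does not justify the null: if the local effect is meant to count, 20% from antibody trials is no longer the rate for a regimen that adds nothing systemically. Nor does the abscopal rate rescue the decision. It has no benchmark or success rule, and it counts shrinkage of any single un-irradiated target lesion at any time, which is not a RECIST response.

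A reader might infer that the protocol says the SBRT lesion counts. It does not; it is silent and so permits it. Some text points the other way: inclusion item 7 treats SBRT and evaluable lesions as separate roles, and the Table 1 notes take biopsies from target lesions while section 5.1 steers easily biopsied lesions away from SBRT. None of this amounts to an exclusion.

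A reader might also take 0.17 and 0.40 as inflated type I error. For the hypothesis as section 6.1 words it they are not: if the regimen's ORR is truly 24% or 28%, the null is false. They are the chances of a positive trial with no systemic gain.

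Finally, the SBRT lesion need not be the patient's largest. It is the largest available one, capped at 5 cm and subject to the other selection principles.

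**Conclusion.** The point holds in this form: endpoint and null are not like-for-like, and following the protocol as written can bias the 17/56 decision only towards success. Under the assumed q of 2.5% to 10%, the chance of a positive trial with no out-of-field gain is 0.09 to 0.40, against 0.043 with no local contribution. The direction follows from the documents. The size does not, because it rests on q and on how far the SBRT lesion dominates each patient's diameter sum.

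It would go too far to say that local shrinkage alone can make the trial positive. The scenarios above need a systemic ORR of 20% underneath, and new lesions or progression elsewhere still block a response.

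**What to change.** In sections 2.1 and 6.5.1, state that the SBRT lesion is not a target lesion for the primary ORR and the 17/56 rule, and that it is followed only for progression. In inclusion item 7, require the out-of-field lesion to be measurable rather than evaluable. Report the all-lesion ORR as supportive. Target lesions are chosen at baseline, so this belongs in the protocol's endpoint definition.

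The cost is protocol wording and one lesion flag in the case report form; the scans are the same. The observed ORR may be lower, and a few patients without a measurable out-of-field lesion become ineligible. The sponsor must also reaffirm 38% as the out-of-field target, since the power of 0.908 depends on it.

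If whole-regimen ORR is kept as primary, say so explicitly, justify the 20% null or raise it for the local SBRT contribution, and restate the rule, power and sample size. For example, an assumed null of 25% needs 20/56, and power at 38% falls to 0.685 with 56 patients.
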